#### Blood Samples

Blood samples will be collected at baseline and closeout visits. These samples will be stored at –20 ℃ until analysis. Laboratory analysis will include hemoglobin, mean corpuscular volume, mean corpuscular hemoglobin, albumin, prealbumin, C-reactive protein, creatinine, prothrombin time, neutrophil-lymphocyte ratio, IL-6, IL-10, and TNF-α levels.

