#### Fecal Samples

Fecal samples will be collect at baseline and closeout visits. Patient will collect the samples at home and deliver them to the clinic within 4 hours of collection. Again, samples will be frozen at –20 ℃ until analysis. Fecal sample analysis will start with a high-quality DNA extraction. The analysis will continue with the bacterial 16S ribosomal RNA gene being sequenced on a MiSeq benchtop sequencer (Illumina Inc). Finally, microbiome composition will be defined using metagenomic species and a database with >200,000 strains.

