#### Inferential Statistics

We will apply inferential statistics to identify differences between the control and experimental groups. In general, dichotomous variables will be compared with chi-square tests, whereas qualitative variables with more than 2 categories will be compared with analysis of variance tests. Continuous variables will be compared with *t* tests for independent samples or Mann-Whitney *U* tests if they do not meet normality. *P*<.05 will be considered statistically significant. More specifically, to analyze the outcomes of the study the following statistical methodology will be performed:

We will analyze the complication rate after surgery in the 2 intervention groups. We will base this analysis on severity and type of complication. After stratification by tumor location, we will use chi-square tests to identify significant differences between the 2 groups. Risk ratio and 95% confidence interval will be used to describe the differences found.We will describe adverse events reported in each group. To find significant differences between the 2 groups, chi-square tests will be used after stratification by tumor location. Risk ratio and 95% confidence interval will be used to describe the differences found.Diversity and composition of the gut microbiota will be analyzed in the 2 groups using McNemar tests and *t* tests to identify significant differences between the groups.Inflammatory differences between the 2 intervention groups will be analyzed with *t* tests if variables meet normality or Wilcoxon tests if variables do not meet normality. We will also analyze the dynamic changes of the neutrophil-lymphocyte ratio in the 2 intervention groups.Differences in dietary pattern and quality of life will be analyzed with McNemar tests for qualitative variables and *t* tests for quantitative data.We will perform a univariate analysis to identify any associations between impact of the microbiome, inflammatory and dietary patterns, and surgery complications. We will perform a multivariate regression with the significant variables found. In addition, the model fit will be assessed using a likelihood-ratio test, area under the receiver operating characteristic curve, Akaike information criterion, and Bayesian information criterion, and we will then validate the model designed using the bootstrap method.

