Finally, we will perform a causal mediation analysis to measure the direct and indirect effects of Micodigest 2.0 on colorectal surgery complications. We will include as mediators the variables related to complications after surgery. This analysis will also show the total effect of other variables on colorectal surgery complications.

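### If taxa are tested one by one, the single P<.05 rule admits chance findings to the between-arm microbiome results and, through a separate screen, to the complication models

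*Protocol article*

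**What the plan says.** All the analysis rules are in the Inferential Statistics section of the protocol article.

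- **Threshold.** After naming the general tests, the section says that P<.05 "will be considered statistically significant". It then lists the analysis of each outcome and gives no other threshold.
- **Microbiome comparison.** "Diversity and composition of the gut microbiota will be analyzed in the 2 groups using McNemar tests" and t tests, with the aim of finding significant differences between the groups. No global test of composition is named. Under Fecal Samples, "microbiome composition will be defined using metagenomic species and a database with >200,000 strains".
- **Screen and regression.** Microbiome, inflammatory and dietary variables are each examined for association with surgical complications. Then: "We will perform a multivariate regression with the significant variables found". Fit is judged by a likelihood-ratio test, AUC, AIC and BIC, and the resulting model is validated by bootstrap.
- **Mediation.** "We will include as mediators the variables related to complications after surgery". No P value is attached to this sentence.

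The Introduction lists the microbiome analyses as secondary objectives.

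**The concern.** The only tests named for composition are univariate, while composition is described by species. The natural reading is therefore one test per taxon, each judged at P<.05. With many taxa and no true effect, that rule produces positive results in proportion to the number tested.

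Significance is also used here to select variables. The screen against complications decides what enters the regression, and it appears to decide what is treated as a mediator of the product's effect. Chance associations picked there would be reported as predictors of complications or as part of the mechanism, from models resting on few events. The Discussion expects these results to point to risk factors and to inform later trials, so false entries would have consequences.

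**Working it through.** **Inputs**

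- Threshold .05 (Inferential Statistics).
- Complication rate 40% under control and a 50% relative reduction, hence 20%; 64 evaluable patients per arm; 10% dropout; 144 in total (Sample Size).
- Number of taxa, m: not given. Assumed values are 20, 50, 100 and 200. The 200,000 strains are the size of a reference database, not a number of tests.

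**The plan's own figures.** The article gives no error rate for the microbiome or other secondary analyses, so there is none to reproduce. The inflation for dropout does reproduce: 64 / 0.90 = 71.1, rounded up to 72 per arm, and 2 × 72 = 144.

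**Step 1: between-arm comparison, no true effect.** Expected false positives = 0.05 × m, whatever the correlation between taxa. Chance of at least one = 1 − 0.95^m if the tests are independent.

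| m (assumed) | Expected false positives | P(at least one), independent |
|---|---|---|
| 10 | 0.5 | 40% |
| 20 | 1.0 | 64% |
| 50 | 2.5 | 92% |
| 100 | 5.0 | 99.4% |
| 200 | 10.0 | >99.9% |

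Three or more expected false positives require m = 3 / 0.05 = 60 tests or more. A simulation with 64 patients per arm and a correlation of 0.3 between taxa left the mean counts essentially unchanged (0.95, 2.6, 5.1 and 10.2 for m = 20 to 200). It lowered the chance of at least one to 52%, 80%, 96% and 99%.

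**Step 2: screen against complications.** If this is also run taxon by taxon at P<.05, the same formula applies. In simulation with 30% of 128 patients having a complication, the mean number of null taxa selected was 1.0, 2.5, 5.0 and 10.0 for m = 20, 50, 100 and 200.

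**Step 3: overlap.** Taxa falsely positive in both analyses: about m × 0.05 × 0.05 = 0.05, 0.125, 0.25 and 0.5. The simulation gave 0.04, 0.12, 0.24 and 0.47. The two sets of false positives are almost entirely different taxa.

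**Step 4: events behind the models.** At the design rates, 64 × 0.40 + 64 × 0.20 = 25.6 + 12.8 = 38.4 complications among 128 patients. Five noise variables alone would leave 38.4 / 5 = 7.7 events per variable, and ten would leave 3.8. If the product had no effect and both arms ran at 40%, there would be 51.2 events, giving 10.2 and 5.1.

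**Step 5: effect of the remedy.** With Benjamini-Hochberg at 5% and no true effect, the simulated chance of any false taxon was about 4% to 5%, and the mean number was 0.05 to 0.15, over m = 20 to 200 and correlations of 0 and 0.3.

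**The case against.** The strongest reply is that this is a condensed article about secondary outcomes. Multiplicity control for high-dimensional data is often left to an analysis plan, and a conventional sentence about P<.05 does not exclude adjustment. That stands against any complaint resting only on a missing correction. It does not answer what the article states: a general threshold and a rule that significant variables enter the regression. A later plan would have to override that rule, not merely add detail.

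A reader might infer that false between-arm taxa are carried into the complication and mediation models. The article does not say so. A separate screen against complications selects the regression variables, and Step 3 shows how little the two sets overlap.

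A reader might also conclude that several false taxa are certain. Testing by taxon is an inference, though a natural one, and the number of tests is not given. At 20 tests the expectation is one, and at 10 it is half of one.

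The argument might be stretched to every other secondary outcome. A rough count of 18 non-microbiome measures (12 blood analytes, 5 nutritional measures, 1 quality-of-life score) gives 18 × 0.05 = 0.9 expected false positives and 1 − 0.95^18 = 60% for at least one. These measures are few and related, and formal adjustment for them is debatable.

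The bootstrap is a real safeguard, but a partial one. It is applied to the model once built, repetition of the screen within resamples is not stated, and no validation is described for the mediation analysis.

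**Conclusion.** The concern holds in a limited form. Followed as written, with taxa tested singly and no true effect, the plan would yield about 1, 2.5, 5 or 10 false positives between arms for 20, 50, 100 or 200 taxa. It would yield as many again, independently, in the complication screen.

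The screen matters more, because it fills the regression and, as the mediation sentence implies but does not say outright, the mediator set, with about 38 expected events.

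The size depends on the assumed number of taxa and on testing by taxon. The chances of at least one false positive also assume independence; the expected counts do not. The primary comparison of complication rates keeps its type I error. This should be corrected before analysis, but it does not threaten the main result.

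**What to change.** 1. For taxon-level tests, replace raw P<.05 with Benjamini-Hochberg control at a stated false-discovery rate, both between arms and in the screen against complications. State the taxonomic level and which taxa form each family of tests.
2. Let only variables that pass this control, or are named in advance on substantive grounds, enter the regression and the mediation analysis.
3. Repeat the whole screen inside each bootstrap resample, so that the validation covers the selection as well as the fit.
4. Report the remaining secondary P values as exploratory, without requiring formal adjustment.

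This changes analysis wording only and needs no further patients or data. The price is that fewer taxa will be declared different, including some with real effects, and fewer variables will enter the models.

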Fungal polysaccharides have attracted attention because of their role in gut microbiota modulation. This type of polysaccharide could reduce pathogen levels and stimulate the growth of beneficial microorganism [24]. As an example, some Basidiomycetes like *Ganoderma lucidum*, *Pleurotus eryngii*, or *Hericium erinaceus* have shown prebiotic activity in animal models [25-27]. In vitro and in vivo studies have shown that polysaccharides from fungi can regulate the microbiota through the fermentation of polysaccharides into short-chain fatty acids [24]. Human studies have also shown a stability for polysaccharides of more than 90% and a capability for stimulating *Lactobacillus* greater than the capability described for other prebiotics [28]. The beneficial effects of fungal polysaccharides is also shown in a randomized study comparing a diet for 10 days based on *Agaricus bisporus* or animal protein. Patients receiving a diet based on fungi showed more Bacteroidetes and fewer Firmicutes [29].

In addition to the beneficial effects of prebiotic activity, fungal polysaccharides have also shown anti-inflammatory activity [27,30]. Polysaccharides isolated from *Ganoderma* and *Lentinula edodes* have shown +immunomodulatory activity in colitis animal models through the production of nitric oxide, tumor necrosis factor alpha (TNF-α), and interleukin-6 (IL-6) [24]. Other examples are the effects of Basidiomycetes extract on the immunological function of inflammatory bowel disease patients and the ability of *G lucidum* to reduce the levels of pro-inflammatory cytokines in CRC patients [31,32]. In addition, some studies show that a combination of different fungal extracts is necessary to maximize the immunological function of different Basidiomycetes [33,34]. Hence, it seems that this combination could send multiple stimuli to the immune system, increasing intracellular reactions and interactions [35-37].

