### Intervention

Patients will be randomized into 2 treatment groups: arm A (control) patients will be treated with placebo before surgery in the same way and timing as the nutraceutical and arm B (experimental) patients will be treated with Micodigest 2.0 before surgery.

The Hifas da Terra company will provide Micodigest 2.0 as 30 capsules and 300 mL syrup with a syringe to measure doses. The drinkable syrup consists of organic extracts from *G lucidum*, *A blazei*, *G frondosa*, *H erinaceus*, *Pleutorus eryngii*, *P ostreatus*, *Myrciaria dubia*, and purified water, raw agave, and natural aroma. The clear vegetable capsules contain *Levilactobacillus brevis*, *Lactiplantibacillus plantarum*, magnesium stearate, silicon dioxide, and extract from *G lucidum*. This treatment is a dietary supplement that has been available since 2016; no adverse effects have been reported. The treatment dose will initiate with 10 mL/day and 1 capsule/day (before breakfast or before lunch) for 7 days and increase to 20 mL/day and 2 capsules/day (10 mL + 1 capsule before breakfast and 10 mL + 1 capsule before dinner) until surgery admission (4-6 weeks).

In the same way, the Hifas da Terra company will supply placebo as 30 capsules and 300 mL syrup with a syringe to measure doses. The drinkable syrup consists of purified water, natural aroma, and agave nectar. This syrup also includes peptin and guar gums as gelling agents and potassium sorbate as preservative. The capsules contain hydroxypropyl methylcellulose and silicon dioxide as anticaking agents and microcrystalline cellulose as a gelling agent. The treatment dose will initiate with 10 mL/day and 1 capsule/day (before breakfast or before lunch) for 7 days and increase to 20 mL/day and 2 capsules/day (10 mL + 1 capsule before breakfast and 10 mL + 1 capsule before dinner) until surgery admission (4-6 weeks).

The assigned study intervention will end if allergic reactions or any serious adverse events are reported. Additionally, patient withdrawal will be a criteria for discontinuing any intervention.

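### Gut microbiota composition from 16S data is given only McNemar and t tests; run on untransformed shares, a rise in an abundant taxon shows up as falls in taxa that did not change

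*Protocol article*

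**What the plan says.** The second of the secondary objectives at the end of the Introduction is the effect of the product on fecal microbiome composition and diversity. Under Inferential Statistics the method is stated in one sentence: "Diversity and composition of the gut microbiota will be analyzed in the 2 groups using McNemar tests and" *t* "tests to identify significant differences between the groups". Diversity and composition are treated alike, and no test of the community as a whole is named. The general rule earlier in that section replaces the *t* test by Mann-Whitney *U* "tests if they do not meet normality", and the threshold is P<.05.

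Fecal Samples gives the assay: "the bacterial 16S ribosomal RNA gene being sequenced on a MiSeq benchtop sequencer", after which "microbiome composition will be defined using metagenomic species and a database with >200,000 strains". No qPCR, spike-in or other measure of total load is described. Nothing says whether counts, shares or log-ratios will be tested.

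**The concern.** Without a measure of load, 16S reads give each taxon's share of the sample, and the shares sum to one. If one abundant taxon grows, every other share must fall, even where the bacteria behind it are unchanged. A separate *t* test on each share would flag such falls, all in the same direction. Correcting for multiple testing does not remove a shared directional shift.

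The pattern matters here because the Introduction cites a diet study in which "Patients receiving a diet based on fungi showed more Bacteroidetes and fewer Firmicutes". A rise in Bacteroidetes alone would produce that picture on the share scale and could be read as two effects. At stake is the interpretation of a secondary objective.

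The use of McNemar, a test for paired data, to compare two independent groups is a separate fault in the same sentence and is not the subject of this point.

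**Working it through.** **Inputs from the article.** 64 evaluable patients per arm (Sample Size; 64/0.90 = 71.1, rounded up to 72, and 2 × 72 = 144 recruited), 1:1 allocation, P<.05. The article gives no figure for the microbiota analysis itself, so there is none to reproduce.

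**Assumptions, not in the article.** Number of taxa, share of the rising taxon, fold rise, and between-patient SD on the log scale. They are varied below.

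**Step 1: arithmetic.** If a taxon with share *p* rises *f*-fold and nothing else changes, every other share is multiplied by 1/(1 − p + pf).

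| Share *p* | Fold *f* | Factor | Change in unchanged taxa |
|---|---|---|---|
| 30% | 2 | 1/1.30 = 0.769 | −23% |
| 30% | 3 | 1/1.60 = 0.625 | −37.5% |
| 10% | 2 | 1/1.10 = 0.909 | −9% |
| 1% | 5 | 1/1.04 = 0.962 | −4% |
| 0.1% | 10 | 1/1.009 = 0.991 | −0.9% |

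**Step 2: what two-sample *t* tests on shares report.** Log-normal loads were simulated for 64 patients per arm and 60 genera, converted to shares, with only the dominant genus (30%) rising. Percentage of unchanged genera with P<.05:

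| Log-SD | Dominant genus doubled | Tripled |
|---|---|---|
| 0.8 | 23% | 57% |
| 1.0 | 13% | 30% |
| 1.5 | about 5% | about 8% |

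Wherever there is material inflation, nearly all flagged genera are falls. If instead a genus at 1% rises 5-fold, the rate stays at about 5%.

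A separate run with 50 taxa agrees. At log-SD 1.0, a 30% taxon doubled or tripled gives 12.8% or 30.8%, a 10% taxon gives 5.8% or 9.9%, and no rise at all gives 4.4% to 4.8%.

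**Step 3: the stated fallback.** In the 60-genus case at log-SD 0.8, Mann-Whitney tests on shares flag about 31% (doubled) and 74% (tripled), so the switch for non-normal data is no better than the *t* test.

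**Step 4: the same *t* test on another scale.** On centred log-ratio values the rate for unchanged taxa is about 5% in all these one-taxon scenarios (4.9% to 5.7% in the 50-taxon run). The problem therefore lies in the scale, not in the *t* test.

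**Step 5: phylum level.** Assume Firmicutes 50%, Bacteroidetes 40%, other 10%, and log-SD 0.6. If Bacteroidetes load rises 1.25-, 1.5- or 2-fold and Firmicutes load is unchanged, a *t* test on the Firmicutes share calls it reduced in about 24%, 65% or 98% of trials.

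**Step 6: limits of log-ratios.** If 20 of the 60 genera double, centred log-ratio *t* tests flag 37% of the unchanged genera. In the phylum case with Bacteroidetes doubled, they flag unchanged Firmicutes in 77% of trials. Centred log-ratios did no worse than shares in any scenario with material inflation, but they do not recover absolute change.

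**The case against.** The strongest reply is that the article never says untransformed shares will be tested, or that testing will be taxon by taxon. A *t* test on log-ratios fits the sentence and, when one taxon moves, holds its error rate. Scale and normalization are details that a condensed article may leave to a fuller document. This stands, and the error rates above are therefore conditional. What remains is that the article does fix the tests for composition, names them jointly with diversity, and points to no log-ratio or community-level method.

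Second, a fall in share is a true fall in relative abundance, and the objective concerns composition, not load. This also stands: the *t* test is wrong only if its result is read as the product having reduced the taxon.

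Third, the size depends on chosen inputs. It fades as between-patient variation grows and vanishes for rare taxa. The only bacteria the product supplies are two lactobacilli in the capsules, whose baseline share is not given; if it is low, their rise would barely move the rest. The cited diet study used *Agaricus bisporus*, which is not among the listed ingredients, so a reader might infer that the trial predicts the Bacteroidetes and Firmicutes pattern, but the objectives do not say so.

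A reader might also infer that falsely flagged taxa would be carried into the complication model and the mediation analysis. The article does not support that: variables enter the model through univariate association with complications, and mediators are the variables related to complications. Neither step selects on a difference between arms.

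**Conclusion.** The point holds in conditional form. The article assigns McNemar and *t* tests to composition measured by an assay that yields relative information only. If shares are tested untransformed and an abundant taxon rises, many unchanged taxa will be flagged as reduced. With a 30% genus doubled or tripled, this is 23% or 57% of unchanged genera at log-SD 0.8, declining to about 5% or 8% at 1.5. It does not arise for a 1% taxon rising 5-fold. These figures rest on assumed shares, fold rises and SDs.

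A reader might go further and conclude that the plan, followed as written, will report false reductions. That is not supported, because the scale is not stated. Alpha-diversity indices are not affected in the same way. The objective is secondary and the primary conclusion is untouched, so this change is worth making but is not critical.

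**What to change.** Replace the single sentence on the microbiota by the following:

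- **Alpha-diversity indices:** keep *t* tests or linear models.
- **Overall composition:** one PERMANOVA on Aitchison distance between arms at closeout, with permutations restricted within tumor location, the trial's stratification factor.
- **Individual genera:** linear models on centred log-ratio abundances, or ANCOM-BC.
- **Bacteroidetes and Firmicutes:** one log-ratio, without saying which phylum moved, and no separate tests of the two shares.
- **Interpretation:** state that all results are relative, and that log-ratio methods reduce but do not remove the bias when many taxa shift.

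The cost is a change of wording and freely available R packages; R is already used for the randomization list. The drawback is that log-ratios are less familiar to clinicians. If the full analysis plan already specifies log-ratio methods, it is enough to bring this sentence into line with it.

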### Sample Size

We designed the study on the basis that the complication rate in the nonintervention arm is 40% and that a 50% reduction would be clinically relevant. Assuming a β error of .80 and an 𝛼 error of .05, 64 patients should be included in each arm. Accounting for a dropout rate of 10%, it would be necessary to include a total of 144 patients (72 patients in each group). The sample size calculation was performed with the Ene 3.0 (GlaxoSmithKline SA) statistical software. A medical doctor will explain the benefits of participating in the study to the patients at the digestive oncology consultation to reach the target sample size.

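### Selecting predictors by univariate significance and then bootstrapping the finished model can make a model with no predictive value look validated, and mediators are chosen by the wrong criterion

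*Protocol article*

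**What the plan says.** Under Inferential Statistics, the protocol article sets P<.05 as its general significance threshold. Its last listed analysis looks for univariate associations of microbiome, inflammatory and dietary patterns with surgical complications. The selection rule follows: "We will perform a multivariate regression with the significant variables found". Fit is judged by a likelihood-ratio test, the area under the ROC curve, AIC and BIC, and then "we will then validate the model designed using the bootstrap method".

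A causal mediation analysis of the product's effect on complications comes next. Its mediators are chosen as follows: "We will include as mediators the variables related to complications after surgery". The same paragraph adds: "This analysis will also show the total effect of other variables on colorectal surgery complications".

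Every step uses the same trial data. The Sample Size section fixes how much information these contain: it assumes that "the complication rate in the nonintervention arm is 40% and that a 50% reduction would be clinically relevant", with 64 evaluable patients per arm and 144 recruited in total.

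**The concern.** Three separate statements are involved.

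- **Predictors.** Variables that cross P<.05 in a small data set are partly there by chance, and their estimated effects are inflated because they were selected for being large. If the bootstrap starts from the model already selected, it corrects for fitting the coefficients but not for the search that found the variables.
- **Mediators.** A mediator has to be something that treatment changes and that in turn affects the outcome. The stated rule looks only at the second link. Taken literally, it admits variables that the product cannot change, and it can drop a plausible mediator whose relation to complications does not show up with few events.
- **Other variables.** A mediation analysis splits the effect of the randomized product into direct and indirect parts. Nothing else in the model is randomized, so it does not identify total effects of other variables.

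This analysis serves the last secondary objective in the Introduction. Under Principal Findings, the article expects it to identify risk factors and to help design further studies. An AUC presented as validated, or a list of microbial or inflammatory predictors, could therefore be carried forward when much of it reflects the search.

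**Working it through.** **1. The plan's own figure.** Inputs from Sample Size: 40% against 20%, alpha .05, and .80, which the article calls a β error and which is read here as power. With pooled variance, no continuity correction and one-sided alpha:

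n = [1.645·√(2·.30·.70) + 0.842·√(.40·.60 + .20·.80)]² / .20² = (1.066 + 0.532)² / .04 ≈ 63.9, so 64 per arm.

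Then 64/.90 = 71.1, so 72 per arm and 144 in total. Both stated figures are reproduced. (A two-sided alpha would give 82 per arm. That is a separate matter and is not used here.)

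**2. Events available.** 64 × .40 + 64 × .20 = 25.6 + 12.8 = 38.4 complications. With no dropout, 72 × (.40 + .20) = 43.2. By the common convention of 10 events per parameter, that supports about 4 parameters.

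**3. Candidates available.** The article gives no number. Blood Samples lists 12 analytes, taken at baseline and at closeout. Nutritional Evaluation adds anthropometry and the PG-SGA. Fecal Samples defines composition at the level of metagenomic species. A range of 12 to 100 is therefore assumed.

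**4. False selections.** For k independent null candidates, the expected number is .05k and the chance of at least one is 1 − .95^k.

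| k | Expected false selections | Chance of at least one |
|---|---|---|
| 12 | 0.6 | 46% |
| 20 | 1.0 | 64% |
| 50 | 2.5 | 92% |
| 100 | 5.0 | 99% |

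Real effects are inflated too. With 128 patients and about 30% events, a true odds ratio of 1.2 per SD averages 1.67 among the runs in which it is significant, and a true 1.5 averages 1.78.

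**5. Validation.** Simulation: 128 patients, about 38 events, independent normal noise predictors, t-test screen at .05, logistic model, and optimism-corrected bootstrap AUC. Values are means over runs in which at least one variable was selected. The true AUC is .50. Ranges show repeated simulations.

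| k | Apparent | Bootstrap of the selected model | Bootstrap repeating the screen |
|---|---|---|---|
| 12 | .64 | .63 | .55 |
| 20 | .66 | .65 | .55 |
| 50 | .67–.71 | .65–.69 | .54–.56 |
| 100 | .77 | .73 | .59 |

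At k = 20 the apparent excess over .50 is .16. Bootstrapping the selected model removes .01 of it; repeating the screen removes .11. At k = 100 the excess is .27, and the amounts removed are .04 and .18.

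**6. Mediation.** Simulation: 64 per arm, 20 noise mediators unrelated to treatment or outcome, 4,000 data sets, linear probability model, mediators kept if P<.05 against complications.

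| | All mediators | Selected mediators |
|---|---|---|
| Mean absolute mediator–outcome slope (40% vs 20%) | 0.032 | 0.091 |
| Mean indirect effect (40% vs 20%) | 0.0 points | −0.7 points |
| Joint-significance false positives (40% vs 20%) | 0.3% | 3.5% |
| Mean indirect effect (30% vs 30%) | near 0 | near 0 |
| SD of indirect effect (30% vs 30%) | 0.7 points | 1.7 points |

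The −0.7 points lie in the direction of the total effect of −20 points, and amount to 0.7/20 = 3.5% of it per selected mediator.

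**The case against.** The strongest reply is that the article does not say the screening is left out of the resampling. It says only that the designed model will be validated by bootstrap, and the details could sit in a fuller document. This stands in part. A reader might infer that the plan rules out repeating the selection; it does not. The natural sense of screening, building a model and then validating it is still a bootstrap of the finished model. The choice of predictors by significance is stated outright and does not depend on this reading.

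Second, the number of candidates is assumed, the candidates are simulated as independent noise, and the microbiome could enter as a few diversity measures. That is fair. Correlated candidates would change the values, though not the direction, and the pattern is already visible at 12 to 20 candidates.

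Third, repeating the screen is not a complete cure. It leaves .55 to .59 against a truth of .50. A small simulation with 200 candidates gave .85, .80 and .67, so there only about half of the excess was removed (.18 of .35). This stands, and it is a reason to shorten the candidate list as well.

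Fourth, it is tempting to conclude that the reported indirect effects would be largely artefacts of selection. The figures do not support that. The bias per mediator is small, has a consistent direction only if there is a total effect, and leaves the joint-significance error below 5%. Nor does the article say that baseline values will serve as mediators, since samples are also taken at closeout. Its mediator rule speaks of a relation to complications without repeating a P-value threshold. The weakness is that the rule sets no time point and requires no effect of treatment on the mediator.

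**Conclusion.** The point holds for the secondary prognostic and mediation analyses, with different strength for each part.

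- **Prognostic model: well supported.** With about 38 expected complications and 20 to 100 assumed noise candidates, the procedure as plainly read would report an AUC of about .65 to .73 as bootstrap-validated where the truth is .50, whenever the screen selects anything. This rests on the assumed candidate count and on the screen not being repeated in each resample.
- **Mediators: the criterion is wrong in kind, but the numerical bias is modest.** Relation to the outcome alone does not identify a mediator. The Introduction itself names age, sex and tumor location as risk factors for complications; a literal reading of the rule would admit them, although the product cannot alter them.
- **Total effect of other variables: a conceptual error in the text.** It depends on no assumption about numbers.

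A reader might take this as a threat to the trial's main result. It is not: the comparison of complication rates between the randomized groups uses none of these steps. The changes should be made, but they are not a condition for the primary analysis.

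**What to change.** 1. Replace the P<.05 screen with a short prespecified candidate set sized to the expected events (for example age, PG-SGA, neutrophil-lymphocyte ratio and one diversity index), or with a penalized model such as LASSO or elastic net. If individual taxa are tested, control the false discovery rate.
2. State that every selection step is repeated within each bootstrap resample, and report the AUC corrected in that way. Add that this removes most but not all of the optimism, and less when there are many candidates.
3. Prespecify the mediators as closeout-visit values (for example a diversity index, neutrophil-lymphocyte ratio or C-reactive protein, and PG-SGA), whatever their P value. Adjust for the baseline value of the mediator and for baseline confounders of the mediator–outcome relation, such as age, tumor location and tumor stage as recorded at the first visit.
4. Delete the sentence on the total effect of other variables, or reword it as association.

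The cost is a few sentences of analysis-plan wording and modest programming, with no change to recruitment or data collection. The downside is that fewer variables can be reported and the published AUC will be lower.
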